Appendix G: Leeds Diactylitis Score

[figure not shown]

| Finger / Toe | Circumference
Involved Digit (A) | Contralateral Digit
(or Tables) (B) | Tenderness Score
(C) | Final Score: $\frac{A}{B} \times C$ |
|--------------|-------------------------------------|----------------------------------------|-------------------------|-------------------------------------|
|              |                                     |                                        |                         |                                     |
|              |                                     |                                        |                         |                                     |
|              |                                     |                                        |                         |                                     |
|              |                                     |                                        |                         |                                     |
|              |                                     |                                        |                         |                                     |
|              |                                     |                                        |                         |                                     |
|              |                                     |                                        |                         |                                     |
|              |                                     |                                        |                         |                                     |
|              |                                     |                                        |                         |                                     |
| TOTAL        | 0                                   | 0                                      | 0                       | 0                                   |

Standard reference: Table - hands

| Digit  | Men | Women |
|--------|-----|-------|
| Thumb  | 70  | 58    |
| Index  | 63  | 54    |
| Middle | 63  | 54    |
| Ring   | 59  | 50    |
| Little | 52  | 44    |

Tenderness score: response to squeeze

0 no tenderness

1 tender

2 tender and wince

3 tender and withdraw

Table – feet

| Digit     | Men | Women |
|-----------|-----|-------|
| Great toe | 82  | 72    |
| Second    | 52  | 46    |
| Middle    | 50  | 44    |
| Fourth    | 50  | 44    |
| Little    | 52  | 45    |

[figure not shown]

Appendix H: FACIT-Fatigue Scale

Below is a list of statements that other people with your illness have said are important. Please select one number per line to indicate your response as it applies to the past 7 days.

|                                                                          | Not
at all | A little
bit | Some-
what | Quite
a bit | Very
much |
|--------------------------------------------------------------------------|---------------|-----------------|---------------|----------------|--------------|
| HI7
I feel fatigued
.....                                          | 0             | 1               | 2             | 3              | 4            |
| HI12
I feel weak all over
.....                                    | 0             | 1               | 2             | 3              | 4            |
| An1
I feel listless (“washed out”)
.....                           | 0             | 1               | 2             | 3              | 4            |
| An2
I feel tired
.....                                             | 0             | 1               | 2             | 3              | 4            |
| An3
I have trouble starting things because I am tired
..... | 0             | 1               | 2             | 3              | 4            |

[figure not shown]

|      |                                                                              |   |   |   |   |   |
|------|------------------------------------------------------------------------------|---|---|---|---|---|
| An4  | I have trouble finishing things because I am tired
.....           | 0 | 1 | 2 | 3 | 4 |
| An5  | I have energy
.....                                                       | 0 | 1 | 2 | 3 | 4 |
| An7  | I am able to do my usual activities
.....                                 | 0 | 1 | 2 | 3 | 4 |
| An8  | I need to sleep during the day
.....                                      | 0 | 1 | 2 | 3 | 4 |
| An12 | I am too tired to eat
.....                                               | 0 | 1 | 2 | 3 | 4 |
| An14 | I need help doing my usual activities
.....                               | 0 | 1 | 2 | 3 | 4 |
| An15 | I am frustrated by being too tired to do the things I want
to do
..... | 0 | 1 | 2 | 3 | 4 |
| An16 | I have to limit my social activity because I am tired                        | 0 | 1 | 2 | 3 | 4 |

[figure not shown]

[figure not shown]

## Appendix J: Clinical Laboratory Tests

| Laboratory Testing Profile                                         | Tests Included                                                                                                                                                                                                                                                                                                                                                                                                                                                                                                                                                                                                                                                                                                                                                          |
|--------------------------------------------------------------------|-------------------------------------------------------------------------------------------------------------------------------------------------------------------------------------------------------------------------------------------------------------------------------------------------------------------------------------------------------------------------------------------------------------------------------------------------------------------------------------------------------------------------------------------------------------------------------------------------------------------------------------------------------------------------------------------------------------------------------------------------------------------------|
| Laboratory tests required prior to first study treatment dose only | QuantiFERON TB-gold test (or equivalent IGRA), HIV testing, hepatitis B serology (HBV PCR if required) including hepatitis B surface antigen and antibody and hepatitis B core antibody, hepatitis C serology, HCV antibodies, confirmatory HCV PCR, SARS-CoV-2 PCR, RF, CCP antibodies, FSH, serum pregnancy                                                                                                                                                                                                                                                                                                                                                                                                                                                           |
| Blood Chemistry                                                    | Sodium, potassium, chloride, bicarbonate, total protein, blood urea nitrogen, serum creatinine, albumin, alkaline phosphatase, AST, ALT, total bilirubin, direct bilirubin, indirect bilirubin, calcium, GGT, creatine kinase, hs-CRP                                                                                                                                                                                                                                                                                                                                                                                                                                                                                                                                   |
| Hematology                                                         | Hemoglobin, hematocrit, WBC with differentials (monocytes, eosinophils, basophils, neutrophils, lymphocytes) as an absolute value, RBC count, platelet count, ESR                                                                                                                                                                                                                                                                                                                                                                                                                                                                                                                                                                                                       |
| Urinalysis                                                         | 
Local urine testing
 
Routine urinalysis will be performed locally with urine dipstick test (semi-quantitative “dipstick” evaluation of specific gravity, pH, glucose, protein, bilirubin, ketones, leukocytes, blood).
 
If the dipstick urine test indicates any abnormal findings, the urine sample will be sent to the central laboratory for further assessments, as appropriate (reflex testing).
 
Central lab urine testing (reflex testing)
 
Urine chemistry (albumin:creatinine and protein:creatinine ratios) to be performed if dipstick indicates protein;
 
Microscopy and/or culture to be performed if clinically indicated or if urinalysis results positive (blood, protein or leukocyte esterase/WBC)
 |

|                                                                         |                                                                                                                                                                                                   |
|-------------------------------------------------------------------------|---------------------------------------------------------------------------------------------------------------------------------------------------------------------------------------------------|
| Urinalysis                                                              | Note: Urine hCG pregnancy testing for WOCBP; may be repeated more frequently than indicated if required by local practice, if a menstrual cycle is missed, or if potential pregnancy is suspected |
| Fasting Lipid Panel and Glucose to be performed at Day 1/Week 0 and EOT | Fasting: glucose, total cholesterol, low density lipoprotein, high density lipoprotein, triglycerides,                                                                                            |

Abbreviations: ALT: Alanine aminotransferase, AST: Aspartate aminotransferase, CCP = cyclic citrullinated peptide; EOT: End of Treatment; ESR: erythrocyte sedimentation rate; FSH: Follicle stimulating hormone; GGT: gamma-glutamyl transferase, HBV: hepatitis B virus; HCV: hepatitis C virus; HIV: Human immunodeficiency virus; hs-CRP: high-sensitivity C-reactive protein, IGRA = interferon-gamma release assay; PCR: Polymerase chain reaction; RBC: red blood cells; RF = rheumatoid factor; TB = tuberculosis; SARSCoV2: Severe Acute Respiratory Syndrome Coronavirus 2; WBC: white blood cells; WOCBP = women of childbearing potential

## Appendix K: Exposure adjusted incidence rate

It will be assumed that for each of  $n$  participants in a clinical trial the time  $t_j$  ( $j=1, \dots, n$ ) to the first occurrence of a certain event is observed, or if the event was not experienced, the (censored) time to the end of the observation period for each treatment group. The sequence of first occurrences of an event will be modeled to follow approximately a Poisson process with constant intensity  $\theta$ . The rate

$$T = \sum_{j=1}^n t_j$$

parameter  $\theta$  will be estimated as  $\lambda=D/T$ , where  $T = \sum_{j=1}^n t_j$  and  $D$  is the number of participants with at least one event. The end of the observation period for subjects randomized in Part A to sonelokimab is the last visit date in Part B or study discontinuation date. The end of the observation period for subjects randomized to placebo or Adalimumab will be the first dose of Part B study medication or study discontinuation if discontinued during Part A. The start of the observation period of sonelokimab for subjects who were randomized to placebo or Adalimumab in Part A will be the first dose of Part B study medication.

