| Derivation of Duration                   |                                                                                                                                                                                                                                                                                                                                                 |
| Study day at any visit                          | Date of interest – date of first dose of study drug. One day is added if this difference is $\geq 0$ .                                                                                                                                                                                                                                          |
| Duration of Exposure (Days) for Part A          | Date of Week 12 or EOT visit, whichever occurs first – Date of first randomized study medication intake at baseline + 1.                                                                                                                                                                                                                        |
| Duration of Exposure (Days) for Part B          | Date of Week 24 or EOT visit, whichever occurs first – Date of first study medication intake for Part B + 1                                                                                                                                                                                                                                     |
| Duration of Exposure (Days) for Part A+B        | Date of Week 24 or EOT visit, whichever occurs first – Date of first sonelokimab intake + 1                                                                                                                                                                                                                                                     |
| Drug Compliance                          |                                                                                                                                                                                                                                                                                                                                                 |

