- Sonelokimab 120 mg Q2W→sonelokimab 120 mg Q4W;
- Sonelokimab 120 mg Q2W→adalimumab 40 mg Q2W;
- Sonelokimab 60 mg Q2W→sonelokimab 60 mg Q4W;
- Sonelokimab 60 mg Q2W→sonelokimab 120 mg Q4W;
- Sonelokimab 60 mg Q4W→sonelokimab 60 mg Q4W;
- Sonelokimab 60 mg Q4W→sonelokimab 120 mg Q4W;
- Placebo→sonelokimab 120 mg Q4W;
- Adalimumab 40 mg Q2W→adalimumab 40 mg Q2W;
- Adalimumab 40 mg Q2W→sonelokimab 120 mg Q2W.
- Total sonelokimab (safety tables only)

**Part A+B:** For Part A+B no statistical testing will be performed. Summary statistics will be based on the data collected from the visit Week 0 to Week 24. Part A+B tables will only be presented for adverse events.

Unless otherwise stated, the summary statistics will be presented for the following treatment groups:

- Placebo (Part A only)
- Total Sonelokimab 120mg
- Total Sonelokimab 60mg
- Total Adalimumab 40mg Q2W
- Total Sonelokimab

For the total groups they will have different subjects potentially for Part A and Part B and subjects will only have results shown for the Part when they took the relevant treatment.

All participant data, including those derived, will be presented in individual participant data listings. Unless otherwise stated, unscheduled visit results will be included in date/time chronological order, within participant listings only. All listings will be sorted by treatment group, investigational site, participant number, date/time, and visit. The treatment group as well as participant's sex, age and race will be stated on each listing. Unless otherwise stated, safety data listings will be based on SAF and efficacy data listings will be based on FAS.

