## 8.5 Extent of Exposure

Extent of exposure will be listed and summarized using the SAF separately for Part A and Part A+B and SAF-B for Part B.

For Part A+B, only two groups will be presented:

- Sonelokimab 120 mg,
- Sonelokimab 60 mg.

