## 8.9 Safety Analyses

For all the safety endpoints, no formal statistical testing will be performed. Safety summaries will be presented by treatment group separately for the Part A (SAF), Part B (SAF-Part B), and Part A+B (SAF).

For Part A, 6 groups will be considered:

- Sonelokimab 120 mg (Q2W),
- Sonelokimab 60 mg (Q2W),
- Sonelokimab 60 mg (Q4W),
- Placebo,
- Adalimumab 40 mg (Q2W),
- Total sonelokimab.

For Part B and follow-up period, 10 groups will be considered:

- Sonelokimab 120 mg Q2W→sonelokimab 120 mg Q4W;
- Sonelokimab 120 mg Q2W→adalimumab 40 mg Q2W;
- Sonelokimab 60 mg Q2W→sonelokimab 60 mg Q4W;
- Sonelokimab 60 mg Q2W→sonelokimab 120 mg Q4W;
- Sonelokimab 60 mg Q4W→sonelokimab 60 mg Q4W;
- Sonelokimab 60 mg Q4W→sonelokimab 120 mg Q4W;
- Placebo→sonelokimab 120 mg Q4W;

- Adalimumab 40 mg Q2W→adalimumab 40 mg Q2W;
- Adalimumab 40 mg Q2W→sonelokimab 120 mg Q2W.
- Total sonelokimab

For Part A+B, 5 groups will be considered:

- Placebo (Part A only)
- Total Sonelokimab 120mg
- Total Sonelokimab 60mg
- Total Sonelokimab
- Total Adalimumab 40mg Q2W

The placebo group will include all subjects who were randomized to placebo in Part A and will only include Part A summary visits.

The total Sonelokimab 120mg group will include all subjects who were randomized to Sonelokimab 120mg Q2W in Part A and subjects who had Sonelokimab 120mg Q2W or Q4W in Part B. Subjects will only be included for summary visits during the Part they were assigned 120mg Q2W.

The total Sonelokimab 60mg group will include all subjects who were randomized to Sonelokimab 60mg Q2W or Q4W in Part A and subjects who had Sonelokimab 60mg during part B (Sonelokimab 60mg Q2W responders and Sonelokimab 60mg Q4W responders). Subjects will only be included for summary visits during the Part they were assigned Sonelokimab 60mg.

The total Adalimumab 40mg Q2W group will include all subjects who were randomized to Adalimumab 40mg Q2W during Part A and subjects who had Adalimumab 40mg Q2W during part B (Adalimumab 40mg Q2W responders and Sonelokimab 120mg Q2W non-responders).

The total Sonelokimab arm will include subjects who received sonelokimab at any time in the study. Subjects will only be included for summary visits during the Part they were assigned Sonelokimab.

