## 8.9.1 Adverse Events

All AEs will be classified by Primary SOC and PT according to MedDRA Version 25.0 or higher and will be graded according to the National Cancer Institute Common Terminology Criteria for Adverse Events (NCI CTCAE) version 5.0.

AEs will be summarized by SOC and PT using counts and percentage (i.e., number and percentage of participants with an AE). AEs will be sorted by decreasing frequency within each SOC and PT as per the overall column.

Where a participant has the same AE, based on PT reported multiple times, the participant will only be counted once at that PT level. Where a participant has multiple AEs within the same SOC, the participant will only be counted once at that SOC level.

If a participant experiences the same AE more than once with different severity grades, then the event with the highest severity will be tabulated by maximum severity. In addition, AEs with a missing severity will be presented in the summary table under the category of ‘Missing’ and will not be imputed.

TEAEs are defined as any AE occurring or worsening on or after the first dose of study treatment.

TEAEs will be assigned to Part A, Part B and Part A+B using the event start date and time and will be defined as:

- Part A: events started on or after the first dose of study medication for Part A but not after Part B or events present prior to the first dose of study medication for Part A but increased in severity on or after dosing on Part A but not after Part B
- Part B: events started on or after the first dose of study medication for Part B or events present prior to the first dose of study medication for Part B but increased in severity on or after dosing on Part B

For Part A+B treatment emergent AEs relating to the Part when the subject was on the corresponding treatment are considered as TEAE.

Adverse events with an onset on Day 1 which are based upon pre-dose lab tests will be considered as not treatment emergent. These are defined as:

- Adverse events which begin on study day 1 with SOC = “Investigations” or PT in (“Hypercholesterolaemia” “Hyperlipidaemia” “Dyslipidaemia”, “Type V hyperlipidaemia”).
- The latest lab test taken on Day 1 has a time which is before the treatment start time.

Treatment-related AEs are those events with relationship to study drug ‘Related’ as recorded on the CRF. If the relationship to study drug is missing, the AE will be considered as treatment related.

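### SAP Appendix K sets exposure-adjusted person-time by Part A randomized arm, while the Part A+B safety groups and their events follow the drug taken in each Part

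*Combined protocol and SAP*

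**What the plan says.** Protocol 12.3.4.1 requires TEAE incidence for Part B and for the combined period to be adjusted for time on study treatment. SAP 8.9.1 asks for treatment years and EAIRs for Part A, Part B and Part A+B. It refers to Appendix J, but the method stands under the heading Appendix K. The estimator there is λ = D/T, where D is the number of participants with at least one event and T is the summed time to first event or to the end of observation.

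**Groups and events follow the drug taken.** SAP 8.1 says of the total groups that "subjects will only have results shown for the Part when they took the relevant treatment". SAP 8.9 places in Total Adalimumab the "subjects who had Adalimumab 40mg Q2W during part B (Adalimumab 40mg Q2W responders and Sonelokimab 120mg Q2W non-responders". SAP 8.9.1 adds: "For Part A+B treatment emergent AEs relating to the Part when the subject was on the corresponding treatment are considered as TEAE".

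**The clock follows the randomized arm.** Under Appendix K, the end for "subjects randomized in Part A to sonelokimab is the last visit date in Part B or study discontinuation date". For the other two arms it says: "The end of the observation period for subjects randomized to placebo or Adalimumab will be the first dose of Part B study medication". A last sentence starts sonelokimab time at that same dose for those randomized to placebo or adalimumab, without limiting this to those who actually move to sonelokimab.

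**The concern.** Responder status at Week 12 decides the Part B drug, but neither of Appendix K's end rules depends on responder status. A programmer cannot satisfy 8.9 and 8.9.1 together with Appendix K, and would have to choose a rule that nobody prespecified.

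At stake is a safety rate that the protocol requires. If events are taken from 8.9.1 and time from Appendix K, Part B events on adalimumab are divided by Part A adalimumab time alone. That raises the reference drug's rate. The Total Sonelokimab rate moves the other way, because its denominator includes weeks spent on adalimumab.

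**Working it through.** The documents give no person-time or EAIR figure, so there is none to reproduce. I first set the rules side by side, using the Part B allocation in SAP 3.3.

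| Participants | Part B drug | Appendix K clock against the 8.9 group |
|---|---|---|
| Arm 5 responders | adalimumab | Adalimumab time stops at first Part B dose; read literally, a sonelokimab clock starts |
| Arm 1 non-responders | adalimumab | Sonelokimab time runs to last Part B visit; no adalimumab start |
| Arms 2 and 3 non-responders | sonelokimab 120 mg | Consistent for Total Sonelokimab; no split between 60 and 120 mg |
| Arm 5 non-responders, Arm 4 | sonelokimab 120 mg | Consistent |
| Responders in Arms 1 to 3 | sonelokimab, same dose level | Consistent |

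**Inputs.** From the documents: 40 per arm and 12 weeks per Part, so t = 0.230 years and one arm for one Part gives 40 × 0.230 = 9.2 person-years. Assumed, because the documents do not say: Week 12 joint-count responder share r1 = 0.6 to 0.8 in Arm 1 and r5 = 0.5 to 0.7 in Arm 5, and share entering Part B f = 0.75 to 1. No other dropout.

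**Adalimumab, untruncated person-time, in units of 9.2.** By drug taken: 1 + f·r5 + f(1 − r1). Appendix K: 1.
- Low: 1 + 0.75 × 0.5 + 0.75 × 0.2 = 1.525, or 14.0 person-years.
- High: 1 + 0.7 + 0.4 = 2.10, or 19.3 person-years.
- Appendix K: 9.2 person-years. The denominator is short by a factor of about 1.5 to 2.1.

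The missing time belongs to 15 to 28 Arm 5 responders (40·f·r5) and 6 to 16 Arm 1 non-responders (40·f·(1 − r1)).

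**Adalimumab, first-event counting, constant hazard h.** Appendix K time is T = 40(1 − e^(−ht))/h. Events by 8.9.1 are D = 40(1 − e^(−ht)) × [1 + f·r5·e^(−ht) + f(1 − r1)], because an Arm 5 responder with a Part A event adds nothing to D in Part B. D/T is therefore h times the bracket, and the bracket is the overstatement.
- h = 0.5: e^(−0.115) = 0.891. Low 1 + 0.375 × 0.891 + 0.15 = 1.48; high 1 + 0.7 × 0.891 + 0.4 = 2.02.
- h = 3 (about half with an event by Week 12): e^(−0.69) = 0.502. Low 1 + 0.375 × 0.502 + 0.15 = 1.34; high 1 + 0.7 × 0.502 + 0.4 = 1.75.

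Worked case with h = 0.5, r1 = 0.7, r5 = 0.6, f = 1: D/T = 7.97/8.69 = 0.92 per person-year against a true 0.50.

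**Total Sonelokimab, untruncated, same units.** By drug taken: 3 + f(4 + r1 − r5).
- Charitable reading (only Arm 5 non-responders start a sonelokimab clock): the excess is f(1 − r1). Low 0.15/6.225 = 2.4%; high 0.4/6.9 = 5.8%.
- Literal reading (Arm 5 responders also start one): the excess is f(1 − r1 + r5). Low 0.525/6.225 = 8.4%; high 1.1/6.9 = 15.9%.

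**Does another section repair it?** No. The Part A+B exposure in SAP 7.1 is counted from the "Date of first sonelokimab intake + 1" to Week 24 or the EOT visit, with no stop at a switch to adalimumab. SAP 8.5 says "For Part A+B, only two groups will be presented", sonelokimab 120 mg and 60 mg, so adalimumab is absent.

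**The case against.** The best defence is that these are descriptive rates, that no formal comparison with adalimumab is planned, and that 8.9 also reports Part B by treatment sequence. That stands, and it limits the importance of the point.

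A second defence is that events could be counted only inside the Appendix K window. Under a constant hazard the adalimumab rate is then unbiased (4.35/8.69 = 0.50 in the worked case). It covers Part A only, however, although 8.9 defines the group to include Part B.

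Three stronger readings are tempting and are not supported:
- **A fixed percentage error in the 60 mg and 120 mg rates.** Appendix K says nothing on dose level. Any figure would assume that time stays with the randomized dose, whereas 8.9 says of the 60 mg total: "Subjects will only be included for summary visits during the Part they were assigned Sonelokimab 60mg". For 120 mg, 8.9 is itself unclear: it admits Part B Q4W participants, then limits summary visits to the Part on 120 mg Q2W. What stands is a missing rule.
- **US participants who complete at Week 12 have no end date.** Appendix K does not name one, but SAP 3.1 gives them a Week 12 EOT visit, and SAP 7.1 ends exposure at EOT if that comes first.
- **The 1.5 to 2.1 range as the error in the rate.** It is a ratio of untruncated person-time. The estimator stops at first event, so the inflation shrinks as the hazard rises.

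**Conclusion.** The conflict is in the SAP's own text and holds whatever the responder rates. It concerns two sets of participants: Arm 5 responders, whose adalimumab time is cut off at Week 12, and Arm 1 non-responders, whose adalimumab time is counted as sonelokimab time. With events by 8.9.1, the Total Adalimumab EAIR is too high by roughly 1.3 to 2.0 times under first-event counting, and the Total Sonelokimab denominator is too long by about 2 to 6%, or more if the last sentence of Appendix K is read literally. Every size depends on the assumed responder shares, Part B entry and, for the first-event figures, a constant hazard between 0.5 and 3 per person-year. Placebo is handled correctly. The primary and key secondary analyses are untouched, so this is a minor point, but worth correcting because the protocol requires the rate.

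**What to change.** Rewrite the observation-period rule in Appendix K for each Part A+B group. Time at risk starts at the first dose of that group's drug or dose level. It ends at the earliest of first event, first dose of a different active drug (for the 60 mg and 120 mg groups, also the first dose of the other level), last visit, or study discontinuation. Count D in the same windows.

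Arm 5 responders then keep accruing adalimumab time, and Arm 1 non-responders change clocks at their first adalimumab dose. Arm 2 and 3 non-responders are split at their first 120 mg dose but stay continuous in Total Sonelokimab. The last-visit term also covers US completers. Event attribution in 8.9.1 can stay as it is.

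The cost is SAP text and programming, with no added data, visits or participants. The small downside is that switchers contribute time to two groups, as they already do for events under 8.9.
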